##### TMS/fMRI safety questionnaires

These questionnaires will be administered in order to rule out potential contraindications to TMS intervention and/or fMRI exams, such as, history of epilepsy, metal implanted devices, brain or eye injury, pregnancy, stroke, etc.).

##### Clinical measures

Medication use and menstrual status will be assessed based on a questionnaire developed by the authors.

#### Primary outcome measures

The primary outcomes of this study are: (1) the change in the number of BE episodes before and after study treatment (number of BE episodes at baseline subtracted from the number of BE episodes at the end of treatment), as measured by participants recording of binge episodes in the food diary during the previous 15 days to the baseline visit (first rTMS session, T.3) to the end of treatment visit (T.23); (2) the change in “urge to eat” (craving) as measured in a 10 cm VAS (from T3 to T22).

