**Methods/Design:**

Sixty eligible obese females, with binge eating disorder, will be randomly allocated to receive 20 sessions of transcranial magnetic stimulation intervention (*n* = 30) or the sham transcranial magnetic stimulation intervention (*n* = 30) scattered 3 days/week. Thirty eligible controls will complete the baseline assessment. The primary outcome (number of binge eating episodes) will be assed at each treatment sessions, and 8 weeks after intervention completion (follow-up). It is hypothesized that mean weekly binge-eating episodes will be reduced in the intervention group, compared to the sham group, and that the effect will be maintained at follow-up.

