#### Secondary outcome measures

Self report measuresA short and modified version (comprising 8 items) of the Food Craving Questionnaire-Trait (FCQ-T) [59]. The FCQ-T was translated and adapted to Brazilian Portuguese (publication in progress). This instrument investigates various aspects of food cravings across different time periods and situations.Binge Eating Scale (BES) [60]. BE severity will be examined using the BES, which is composed of 16 items and has been translated and validated to Portuguese Change in the total mean score from the baseline visit (T.3) to the end-of treatment evaluation (T.23) and 8-week follow up (T.24) will be compared between the two randomized groups.Three Eating Factor Questionnaire (TEF-Q) [61]. The reduced 21 item version (TEFQ-R21) [62], which has been translated and adapted to Brazilian Portuguese [63] will be used. Overall, the questionnaire evaluates the following aspects: eating cognitive restrain, emotional eating and control over eating.The Loss of Control over Eating Scale (LOCES) [64] is an instrument developed to investigate aspects associated with the loss of control over eating. The scale has been translated and validated to Brazilian Portuguese (publication in progress).UPPS Impulsive Behavior Scale [65] was originally developed with five factors and later reduced to four factors and 45-items [66]. These factors were divided as: a) urgency, tendency to experience strong impulses, b) lack of premeditation, tendency not to think about the consequences of an act before engaging in it, c) lack of perseverance, lack of the ability to stay focused on a task that can be boring or difficult, and d) sensation seeking, tendency to search for activities that are exciting, and openness to try new experiences. The scale is also available in Brazilian Portuguese [67].Depression Anxiety Stress Scales (DASS-21) is a 21-item self-report scale [68] developed to measure the negative emotional states of depression, anxiety and stress during the past week. Each item is rated using a 4-point severity/frequency scale according to the corresponding statement. DASS-21 is available in Brazilian Portuguese [69].Food diary. Participants will be instructed to register complete food intake in a food diary for seven consecutive days before the T.3, T.23 and T.24 visits, and to record BE episodes for 15 consecutive days before the same time points (T.3, T.23 and T.24).Body Shape Questionnaire (BSQ-34). The questionnaire has been validated in patients with eating disorders and includes assessments of body image. The questions related to body shape perception and range from 1 to 6. Higher scores on these scales indicate greater psychopathology. The questionnaire has been translated and validated to Brazilian Portuguese [70].The 12-item Short Form Health Survey (SF-12). This questionnaire measures health-related quality of life, subdivided in two scales – Physical Health Component Summary scales (PCS) and Mental Health Component Summary scales (MCS) [71]. It has been translated into Brazilian Portuguese [72].

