### Sample size and statistical analysis

To detect the change in craving and BE frequency before and after treatment intervention, the following parameters were used to estimate sample size: effect size *f* = 0.31 (supposed to be small), alpha error probability =0.05, power = (1-β error probability) = 0.8, number of groups = 2, number of measurements through the follow-up = 3 and correlation among repeated measurements = 0.5.

Statistical Inferences: Two different types of analyses will be used to evaluate the effectiveness of the rTMS. The first (and standard) method is intention-to-treat (ITT) that assumes that every patient allocated to be intervention actually received it [75]. The other paradigm, CACE estimation method [76, 77] will take into account the compliance status (patient’s adherence to the rTMS).The compliance status is defined here as at least one of 20 session of rTMS; CACE estimation, therefore, provides a realistic effect under non-adherence phenomenon being estimated based on the structural equation modeling. Underlying both paradigms, it will be used growth modeling, which examines the development of individuals on one more outcome variables over the time. In growth modeling (on contrary of repeated ANOVAS), random effects are used to capture individual differences in development. The corrected significance level (Bonferroni) to be adopted due to 32 outcomes will be 0,0015. Such procedure will be carried to avoid false discovered rate due to multiple comparisons. All the statistical inference will be done via Mplus 7.0. In addition, careful fMRI image acquisition and processing will be completed and analyzed taking into consideration the limitations of fMRI studies.

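### The primary outcome is an unadjusted T3-to-T23 change in binge count, but the planned growth model is not tied to that contrast or to the T3 count

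*Protocol article*

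**What the plan says.** Primary outcome measures: the first primary outcome is the change in binge-eating episodes from the first stimulation session (T3) to the end-of-treatment visit (T23), computed as the "number of BE episodes at baseline subtracted from the number of BE episodes at the end of treatment". Secondary outcome measures, under the food diary, gives the recording schedule: participants are "to record BE episodes for 15 consecutive days before the same time points (T.3, T.23 and T.24"). The binge count is therefore a 15-day total at three visits.

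Sample size and statistical analysis: for both the intention-to-treat and the complier analyses, "it will be used growth modeling, which examines the development of individuals on one more outcome variables over the time". The section adds that "In growth modeling (on contrary of repeated ANOVAS), random effects are used to capture individual differences in development". The sizing uses "number of groups = 2, number of measurements through the follow-up = 3" and a correlation of 0.5 between repeated measurements. Tests are to be judged at 0.0015 because of 32 outcomes.

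The abstract puts the hypothesis on another scale: "mean weekly binge-eating episodes will be reduced in the intervention group, compared to the sham group". The Hypothesis section lists maintenance at 8 weeks among the secondary hypotheses, which makes T23 the primary time point.

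**The concern.** The outcome section fixes one quantity, a change between two named visits. The statistical section fixes a method that models a trajectory over three. Nothing says which parameter of the growth model tests the T3-to-T23 change, or how the T3 count enters.

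Two things are at stake. First, if the outcome is analysed as defined, subtracting the baseline carries its full noise into the comparison, although the same T3 data could be used to reduce that noise. With 30 women per arm and a threshold of 0.0015, the trial has little power to spare. Second, a trajectory parameter may answer a different question from the primary one, depending on the time shape chosen.

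**Working it through.** **1. The plan's own sample size.** Inputs from the sample size section: f = "0.31 (supposed to be small), alpha error probability =0.05", "power = (1-β error probability) = 0.8", m = 3 measurements, rho = 0.5. No N is printed there; 60 comes from the overview of the design.

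- Between-groups repeated-measures F test: lambda = f²·N·m / (1 + (m − 1)·rho). At N = 58, lambda = 0.0961 × 58 × 3 / 2 = 8.36 with 1 and 56 df, and power is 0.811. At N = 60, power is 0.824.
- Group-by-time interaction: lambda = f²·N·m / (1 − rho) would need only about N = 20.

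So 60 is reproduced, within two patients, only by the test that averages the three visits, baseline included. That is a third quantity: neither the T3-to-T23 change nor a growth parameter.

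**2. Cost of not adjusting, on the protocol's correlation.** Assume equal variance at T3 and T23, and an effect of 0.62 SD (2f for two groups, 2 × 0.31). In SD² units per patient:

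- raw change: 2(1 − rho) = 2 × 0.5 = 1.00
- baseline-adjusted: 1 − rho² = 1 − 0.25 = 0.75, which is 25% less

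Noncentrality with 30 per arm:

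- raw change: 0.62 / √(1.00 × 2/30) = 2.40 (58 df)
- adjusted: 0.62 / √(0.75 × 2/30) = 2.77 (57 df)

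| alpha | raw change | adjusted | ratio |
|---|---|---|---|
| 0.05 | 65.6% | 77.8% | 1.19 |
| 0.0015 | 19.0% | 30.0% | 1.58 |

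Put as patients, unadjusted change needs 30 / 0.75 = 40 per arm to match an adjusted analysis with 30.

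**3. The same comparison on counts.** The article gives no baseline mean, dispersion or expected sham decline, so these are assumptions: mean 6 episodes per 15 days, log-SD 0.5 between and 0.35 within persons, Poisson counts, 30 per arm, alpha 0.05.

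| sham rate | active rate | raw change | linear, adjusted for T3 | ratio |
|---|---|---|---|---|
| ×0.65 | ×0.38 | 29% | 70% | 2.4 |
| ×0.90 | ×0.525 | 47% | 77% | 1.6 |
| ×1.00 | ×0.60 | 51% | 75% | 1.5 |

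The rate ratio is about 0.58 to 0.60 in every row. What changes the gain is how far the sham arm falls. In the first row a log-link overdispersed count model with log baseline gives 72%, two points above the linear adjusted analysis, so baseline adjustment supplies nearly all of the gain. Type I error was 4% to 6% for all three methods.

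**4. What a straight line would test.** This is conditional, because no time shape is stated. Visits fall at about weeks 0, 7 and 15: treatment lasts about 7 weeks and follow-up is 8 weeks later. The mean time is 22/3 = 7.33 and the sum of squares is 112.67. Least-squares slope weights, multiplied by 7 weeks:

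- T3: −7.33/112.67 × 7 = −0.46
- T23: −0.33/112.67 × 7 = −0.02
- T24: 7.67/112.67 × 7 = +0.48

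An effect of 1 at both T23 and T24 is recovered as 0.46. An effect of 1 at T23 that is gone by T24 is recovered as −0.02. In a simulation with assumed mean 7, sham ×0.6 and active ×0.4 at T23, with the effect lost by T24, the slope was significant in 4.3% of trials, raw change in 21% and baseline-adjusted analysis in 57%.

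**The case against.** The strongest reply is that the criticised analysis is not the one written down. The article does not say that change scores are entered into the growth model, and growth models ordinarily take the repeated values themselves. The T3 count is one of the three measurements, so a growth model with visit as categorical and a common baseline mean would recover about the precision of baseline adjustment. The article does not exclude that model, nor a count distribution. Time shape, distribution and handling of incomplete diaries may sit in an analysis plan that is not shown.

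Most of this stands, and it rules out several stronger readings. A reader might infer that the baseline information is certainly wasted, or that a linear slope is planned; neither is stated. A reader might infer that adjustment would more than double power. On the protocol's own correlation the gain is 1.19-fold at alpha 0.05, and doubling needs a large sham decline that the article does not document. A reader might also infer that counts are low because the diagnostic minimum is one episode per week. That is an eligibility floor, not an expected mean.

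The reply does not remove the mismatch. The definition of the primary outcome as an unadjusted difference is fixed in the text, and so is a method with no stated link to it. A later plan would have to reinterpret one of the two passages.

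**Conclusion.** The point holds as a mismatch between the primary outcome and its analysis, with an avoidable loss of efficiency if the raw change is analysed as defined. The variance reduction of 25% rests only on the protocol's correlation of 0.5 and equal variances. The power figures in step 2 also assume an effect of 0.62 SD and no dropout. The count-scale range, about 1.5-fold to over 2-fold, rests on assumed means, dispersion and sham decline, and should be quoted only as a range. The near-zero weight on T23 applies only if the curve is a straight line. This is a change that should be made, not a defect that invalidates the trial.

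**What to change.** State the primary test for binge eating as the between-arm contrast at T23, adjusted for the T3 count. An equivalent choice is a longitudinal model with visit as categorical and the arms constrained equal at T3. Read T24 as a separate contrast, in line with its place among the secondary hypotheses.

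Preferably use a log-link overdispersed count model with log baseline count, and an offset for completed diary days where these are recorded. Because a 15-day baseline count can be zero (probability exp(−15/7) = 0.12 for a Poisson count at one episode per week), state a small constant to add before taking logs. Keep raw change as a descriptive summary.

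The cost is wording only: the three diary counts are already scheduled, and no patients or visits are added. The effect is then reported as an adjusted difference or a rate ratio; a rate ratio can be converted back to episodes.

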#### Secondary outcome measures

Self report measuresA short and modified version (comprising 8 items) of the Food Craving Questionnaire-Trait (FCQ-T) [59]. The FCQ-T was translated and adapted to Brazilian Portuguese (publication in progress). This instrument investigates various aspects of food cravings across different time periods and situations.Binge Eating Scale (BES) [60]. BE severity will be examined using the BES, which is composed of 16 items and has been translated and validated to Portuguese Change in the total mean score from the baseline visit (T.3) to the end-of treatment evaluation (T.23) and 8-week follow up (T.24) will be compared between the two randomized groups.Three Eating Factor Questionnaire (TEF-Q) [61]. The reduced 21 item version (TEFQ-R21) [62], which has been translated and adapted to Brazilian Portuguese [63] will be used. Overall, the questionnaire evaluates the following aspects: eating cognitive restrain, emotional eating and control over eating.The Loss of Control over Eating Scale (LOCES) [64] is an instrument developed to investigate aspects associated with the loss of control over eating. The scale has been translated and validated to Brazilian Portuguese (publication in progress).UPPS Impulsive Behavior Scale [65] was originally developed with five factors and later reduced to four factors and 45-items [66]. These factors were divided as: a) urgency, tendency to experience strong impulses, b) lack of premeditation, tendency not to think about the consequences of an act before engaging in it, c) lack of perseverance, lack of the ability to stay focused on a task that can be boring or difficult, and d) sensation seeking, tendency to search for activities that are exciting, and openness to try new experiences. The scale is also available in Brazilian Portuguese [67].Depression Anxiety Stress Scales (DASS-21) is a 21-item self-report scale [68] developed to measure the negative emotional states of depression, anxiety and stress during the past week. Each item is rated using a 4-point severity/frequency scale according to the corresponding statement. DASS-21 is available in Brazilian Portuguese [69].Food diary. Participants will be instructed to register complete food intake in a food diary for seven consecutive days before the T.3, T.23 and T.24 visits, and to record BE episodes for 15 consecutive days before the same time points (T.3, T.23 and T.24).Body Shape Questionnaire (BSQ-34). The questionnaire has been validated in patients with eating disorders and includes assessments of body image. The questions related to body shape perception and range from 1 to 6. Higher scores on these scales indicate greater psychopathology. The questionnaire has been translated and validated to Brazilian Portuguese [70].The 12-item Short Form Health Survey (SF-12). This questionnaire measures health-related quality of life, subdivided in two scales – Physical Health Component Summary scales (PCS) and Mental Health Component Summary scales (MCS) [71]. It has been translated into Brazilian Portuguese [72].

Anthropometric measures will be completed as previously described.

##### Biomarkers

Blood serum levels of reactive-C protein, BDNF, adiponectin, TNF-Alpha, IL-6, IL-10, leptin, ghrelin, PYY_3–36_, estradiol and progesterone will be measured in order to analyze changes in inflammatory response, hormones and neurotrophic factors.

##### Cognitive evaluation

The evaluation will include seven cognitive tests investigating executive functions such as, working memory, control inhibition and decision-making, as described in details in Additional file 2: Table S2.

##### Neuroimaging

Neuroimaging scans will be performed on a 3 T Magneton Trio Tim System (Siemens, Germany) scanner. Magnetic Resonance Imaging (MRI) scans will be acquired for the whole brain structure (T1-weighted, 1 mm resolution). Functional Magnetic Resonance Imaging (fMRI) scans for resting state (no task) will be acquired to investigate functional connectivity. T2-weighted echo-planar images (EPI) depicting blood oxygen level dependent (BOLD) contrast will be acquired during the Stroop Word Color Task (SWCT). The SWCT is widely used as an index of attention and executive control [73]. The task requires the ability to actively inhibit a learned response in favor of a more voluntary (and difficult) response. A SWCT block-design of three conditions (control/congruent, neutral and incongruent) will be used during the fMRI. Neuroimaging allows for a deeper understanding of brain structures, patterns and activation. The fMRI exam and the SWCT will be used as tools to investigate brain areas involved in automatic inhibitory responses during the SWCT. Further, the SWCT allows the investigation of differences in activation patterns and connectivity in the PFC during the task [74].

Food Challenge Task (FCT): The task was used and described in previous studies [47]. The FCT requires participants to watch a film clip (2 min.) followed by exposure of food (10 min.), in order to stimulate craving. The current study will only use the film clip to stimulate craving; there will be no food exposure. Participants will also complete the Visual Analogue Scale (VAS) of “urge to eat”, “hunger”, “tension” and “mood” and a short and modified version (comprising 5 items) of the Food Craving Questionnaire-State (FCQ-S) [59], which was translated to Brazilian Portuguese and is in the process of validation. The FCQ-S investigates aspects of food craving in real time. In addition, salivary cortisol samples will be collected along with the FCT to examine potential impact of stress (exposure to food cues).

##### rTMS tolerability and safety

Participants will be provided with a monitoring record and instructed to record any experience of adverse events during the rTMS treatment. The monitoring record will be reviewed before each rTMS session. Tolerability will be based on the number of adverse events reported (grouped per side effect type) and number of dropouts due to adverse events or other reasons. Safety will be measured based on the occurrence of serious adverse events, such as seizures (reported as rare in rTMS studies).

### Sample size and statistical analysis

To detect the change in craving and BE frequency before and after treatment intervention, the following parameters were used to estimate sample size: effect size *f* = 0.31 (supposed to be small), alpha error probability =0.05, power = (1-β error probability) = 0.8, number of groups = 2, number of measurements through the follow-up = 3 and correlation among repeated measurements = 0.5.

Statistical Inferences: Two different types of analyses will be used to evaluate the effectiveness of the rTMS. The first (and standard) method is intention-to-treat (ITT) that assumes that every patient allocated to be intervention actually received it [75]. The other paradigm, CACE estimation method [76, 77] will take into account the compliance status (patient’s adherence to the rTMS).The compliance status is defined here as at least one of 20 session of rTMS; CACE estimation, therefore, provides a realistic effect under non-adherence phenomenon being estimated based on the structural equation modeling. Underlying both paradigms, it will be used growth modeling, which examines the development of individuals on one more outcome variables over the time. In growth modeling (on contrary of repeated ANOVAS), random effects are used to capture individual differences in development. The corrected significance level (Bonferroni) to be adopted due to 32 outcomes will be 0,0015. Such procedure will be carried to avoid false discovered rate due to multiple comparisons. All the statistical inference will be done via Mplus 7.0. In addition, careful fMRI image acquisition and processing will be completed and analyzed taking into consideration the limitations of fMRI studies.

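### The trial is sized for its primary outcomes at alpha 0.05, but the only significance level set for testing is 0.0015, at which 80% power becomes about 36%

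*Protocol article*

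**What the plan says.** All the figures for the sizing and the testing level stand in one section of the protocol article, Sample size and statistical analysis.

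- **Sizing.** The calculation is for craving and BE frequency. The type I error is set by "alpha error probability =0.05". The other inputs are a target power of 80%, an f of 0.31 that the article takes to be small, two arms, three occasions of measurement, and a correlation of 0.5 between occasions. The section does not name the test or print the resulting N. The abstract and the Overview and study design section give 60 randomized patients, 30 per arm in the abstract.
- **Testing.** After describing the intention-to-treat and complier-average analyses, both built on growth models, the section says: "The corrected significance level (Bonferroni) to be adopted due to 32 outcomes will be 0,0015". It does not list the 32 outcomes, exempts none and states no other level for inference.
- **Primaries.** The section Primary outcome measures begins "The primary outcomes of this study are: (1) the change in the number of BE episodes before and after study treatment" and adds the change in urge to eat on a visual analogue scale as the second. The abstract speaks of one: "The primary outcome (number of binge eating episodes) will be assed at each treatment sessions".

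**The concern.** A power statement is tied to the level at which the test is carried out. Here the power is worked out at 0.05, while the only level set for inference is about one thirty-third of that (0.05 / 0.0015 = 33.3). The stricter level is not carried back into the sample size. If it applies to BE episodes and craving, the primary hypothesis shares its error allowance with a long list of questionnaires, biomarkers and cognitive tests, and the chance of confirming a true effect of the planned size is far below what the protocol advertises. The error runs towards false negatives, not false positives. It still bears on whether the trial can do what it was sized to do.

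**Working it through.** **Inputs (protocol article, Sample size and statistical analysis):** f = 0.31, 2 groups, m = 3 measurements, rho = 0.5, alpha = 0.05, power 0.80; N = 60 from the abstract and the Overview and study design section.

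**Step 1. Reproduce the trial size.** For the between-group effect in a repeated-measures ANOVA, the noncentrality is

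lambda = f² × N × m / (1 + (m − 1) × rho), with 1 and N − 2 degrees of freedom.

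Here f² = 0.0961 and 1 + 2 × 0.5 = 2, so lambda = 0.0961 × 3 / 2 × N = 0.14415 × N. Among even N at alpha 0.05:

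- N = 56: power 79.7%
- N = 58: power 81.1%, the smallest that reaches 80%
- N = 60: lambda = 8.649, power 82.4%

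The stated 60 is within two patients of 58.

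**Step 2. Try the other standard readings of the same inputs.** N needed for 80% power at alpha 0.05:

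| Reading of f = 0.31 | N |
|---|---|
| Between-group effect | 58 |
| Group-by-time interaction, or within-subject effect, lambda = f² N m / (1 − rho) | 20 |
| One-df slope, same lambda | 16 |
| Single-measurement ANOVA, lambda = f² N | 84 |
| Interaction without the correlation term | 102 |

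Only the between-group reading gives about 60.

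**Step 3. Apply the testing level.** 0.05 / 32 = 0.0015625, which the article gives as 0.0015. With N = 60 and lambda = 8.649 on 1 and 58 df:

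| Level | Power at N = 60 | N for 80% power |
|---|---|---|
| 0.05 | 82.4% | 58 |
| 0.025 | 73.7% | 70 |
| 0.05/32 = 0.0015625 | 36.4% | 118 |
| 0.0015 | 35.9% | 118 |

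Truncating the level to 0.0015 costs half a percentage point. At 0.0015, 60 patients give 80% power only for an effect of about f = 0.44, against the planned 0.31.

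**Step 4. A check that does not depend on the ANOVA.** Take any one-df test with exactly 80% power at two-sided 0.05 and use the normal approximation. Its expected z is 1.960 + 0.842 = 2.802. The critical value at two-sided 0.0015 is 3.175. Power is Φ(2.802 − 3.175) = Φ(−0.373) = 35.5%.

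**The case against.** **The 36% depends on the model.** This stands as a qualification. The article does not name the test behind its sizing, it plans growth models and sets them against repeated ANOVA, and it defines the first primary as a change from baseline to end of treatment. With f = 0.31, N = 60 and level 0.0015, other tests give other powers:

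- Group-by-time interaction (lambda = 0.0961 × 60 × 3 / 0.5 = 34.6; 2 and 116 df): 98.7%.
- Simple change score, taking f as the end-of-treatment difference (lambda = 0.0961 × 60 = 5.77): about 19%.
- Baseline-adjusted end value, same assumption (lambda = 5.77 / (1 − 0.5²) = 7.69): about 30%.

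The interaction reading would remove the problem, but the same inputs would then call for 20 patients, so it does not explain a trial of 60. Step 4 also shows that if the article's 80% is right for any one-df test, the fall to about 35% follows.

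**Inclusion of the primaries is inferred.** This also stands. The 32 outcomes are not itemised, so a reader should not take it that the article expressly puts the primaries among them. But one level is adopted, nothing is exempted, and if the primaries were meant to stay outside, their testing level is stated nowhere.

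**Stronger readings that the article does not support:**

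- *That the two statements are logically incompatible.* Both can be carried out. The result is less power than stated.
- *That Bonferroni is the wrong tool because the article speaks of false discovery.* Bonferroni also controls the false discovery rate, conservatively. The wording is loose but the method meets the aim.
- *That a negative trial would be uninterpretable.* Estimates and confidence intervals would still inform.
- *That one primary in the abstract against two in the body proves the alpha problem.* It does not. It matters only because the repair must say how many primaries share the alpha.

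**Conclusion.** The point holds: the sample size and the testing rule in the same section use different alphas, and the stated 80% power does not describe the rule as written. Under the one standard variant tried that reproduces the trial size, power at N = 60 falls from 82% to about 36%, and 80% at 0.0015 would take about 118 patients, roughly double.

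This rests on two assumptions: that the primaries fall under the 0.0015 level (the natural reading, not an explicit statement), and that f = 0.31 is the between-group effect. No dropout was allowed for in these figures, and the sizing text mentions none; losses would lower the power further. The mismatch between the two alphas does not depend on the model, but the exact 36% does.

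**What to change.** Take BE episodes and craving out of the 32-outcome correction and state their alpha. Either of these would do:

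1. **Fixed sequence.** Test BE episodes at two-sided 0.05, and craving at 0.05 only if BE episodes are significant. The sizing at 0.05 then applies to BE episodes. BE episodes come first here because the abstract names them as the primary outcome.
2. **Split alpha.** Test each primary at 0.025 and restate the power as about 74% under the between-group model. Holding 80% at that level would need 70 patients.

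Keep a multiplicity correction for the remaining outcomes and say which outcomes it covers; the choice of procedure is the sponsor's. State the number of primaries the same way in the abstract and the body, and name the test behind the sample size. If 0.0015 is to stay for the primaries, say so and restate the power as about 36% under the same model.

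The cost is wording in the analysis section and a protocol amendment, best made before unblinding. Neither option, with the power restated where needed, requires more patients or data. The price is that the primaries no longer share one error budget with the other outcomes, so error control across all 32 together is weaker than under the single Bonferroni level.

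### The multiplicity rule is justified in false-discovery-rate terms but fixed as single-step Bonferroni at 0.0015 for 32 outcomes, which is valid but stricter than the stated aim and needlessly low in power

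*Protocol article*

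**What the plan says.** Two adjacent sentences in the protocol article, under Sample size and statistical analysis, set the rule. The first gives the method and the level: "The corrected significance level (Bonferroni) to be adopted due to 32 outcomes will be 0,0015". The second gives the reason: "Such procedure will be carried to avoid false discovered rate due to multiple comparisons".

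The same section sizes the trial. The purpose given for the calculation is "To detect the change in craving and BE frequency before and after treatment intervention". The effect assumed is "effect size *f* = 0.31 (supposed to be small". The other inputs are a type I error of 0.05, 80% power, two arms, three assessments per patient and a within-patient correlation of 0.5. Overview and study design sets 60 randomised patients, and Randomization sets 1:1 allocation.

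The statistical section does not say which outcomes make up the 32, does not exempt the two primary outcomes from the corrected level, gives no effect size for any secondary outcome, and names no target false discovery rate.

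**The concern.** The false discovery rate is the expected share of false findings among the outcomes declared positive. Single-step Bonferroni bounds something else: the chance that any of the 32 outcomes is falsely declared positive. The plan names the first and fixes a tool for the second.

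Even if family-wise control is what is meant, the single-step form is dominated. Holm's step-down procedure at 0.05 gives the same guarantee under any dependence between outcomes. Its first threshold, 0.05/32 = 0.0015625, is already slightly above 0.0015, and the later ones are larger, so it rejects everything that the fixed level rejects and sometimes more.

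Power is at stake in the part of the trial that the Background and Discussion present as its distinctive value: a programme across behaviour, hormones, inflammation, cognition and brain function, with directional hypotheses for many of these. With the fixed level, true effects in those domains are more likely to be reported as null than the stated aim requires.

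**Working it through.** **1. What the fixed level controls.** 0.05/32 = 0.0015625, which the plan gives as 0.0015. The bound on the family-wise error is 32 × 0.0015 = 0.048. Under independence it is 1 − (1 − 0.0015)^32 = 4.7%. This is family-wise control at just under 5%.

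**2. The plan's own sample size.** The article does not name the test behind its calculation. A between-groups test in a repeated-measures ANOVA has noncentrality

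λ = f² × N × m / (1 + (m − 1)ρ), with 1 and N − 2 degrees of freedom.

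With f = 0.31, m = 3 and ρ = 0.5, this is 0.0961 × N × 1.5.

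- N = 58: λ = 8.36, power 81.1% at alpha 0.05. This is the smallest equal-arm size above 80%.
- N = 60: λ = 8.65, power 82.4% at alpha 0.05.

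The stated 60 is therefore reproduced to within two patients. Other readings do not fit: a within-between interaction needs N = 20, a single-time-point or change-score comparison needs N = 84, and an ANCOVA on one baseline needs N = 64.

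**3. Power per outcome at the fixed level.** With the same model, N = 60 and alpha 0.0015, power is 35.9%.

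**4. Alternatives, by simulation.** There were 20,000 simulated trials per scenario, each with 32 outcomes and t statistics on 58 degrees of freedom. Affected outcomes had noncentrality √8.649 = 2.94. The correlation between outcomes was 0 or 0.3. Two assumptions do not come from the document: every affected outcome has f = 0.31, and the number affected is 5, 10, 16 or 24. Ranges run over the two correlations.

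| Affected, of 32 | Bonferroni 0.0015 | Holm 0.05 | Benjamini-Hochberg q = 0.05 | At least one false positive: Bonferroni | At least one false positive: Benjamini-Hochberg |
|---|---|---|---|---|---|
| 5 | 36% | 37% | 50-51% | 4% | 12-15% |
| 10 | 36% | 38% | 60-61% | 3% | 18-23% |
| 16 | 36% | 39% | 67-69% | 2-3% | 21-27% |
| 24 | 36% | 41% | 73-76% | 1% | 18-22% |

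The realised false discovery rate was 0.1-1.9% with Bonferroni and 1.2-4.2% with Benjamini-Hochberg, so both stay below 5%.

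**5. Sensitivity to family size.** If the 32 include the two primaries and the secondary family is 30, Benjamini-Hochberg power is 48-49% with 4 affected (47-48% for a family of 32) and 73-77% with 24 affected (72-76%), over correlations of 0 to 0.5. The comparison does not depend on which count is meant.

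**The case against.** The strongest reply is that the purpose sentence is loose wording for avoiding false positives. It sets no target rate, whereas method, level and number of outcomes are explicit and valid. Read literally, the aim is still met, since family-wise control implies control of the false discovery rate. Choosing the stricter error rate is a legitimate design judgement. All of this stands as a defence of validity. It does not defend the text: if the false discovery rate is the aim, the method is stricter than needed, and if family-wise control is the aim, the sentence is wrong and Holm is available without loss of error control.

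Three stronger readings are tempting and not supported.

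- A reader might infer that the rule inflates error. It does the reverse; it is conservative.
- A reader might compute power from one comparison of 30 with 30 at d = 2 × 0.31 = 0.62. That gives 19% at 0.0015 and, for Benjamini-Hochberg, 27% (5 affected) to 48-50% (24 affected). It drops the three measurements and the correlation that the plan states, has only 66% power at 0.05, and so contradicts the plan's own sizing.
- A reader might call these the planned powers for secondary outcomes. The plan gives f = 0.31 only for craving and binge-eating frequency, and it does not confine 0.0015 to the secondaries.

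It is also fair to say that Holm's gain is small, at 1 to 5 percentage points. The large gain needs a change of error rate, and that has a real price in isolated false positives.

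Sizing at 0.05 while testing at 0.0015 is a separate matter in the same section, and this point does not rest on it.

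**Conclusion.** The point holds as a mismatch between stated aim and chosen method, with avoidable loss of power. It is not a fault of validity. On the repeated-measures model that reproduces the sample size, the fixed level gives about 36% power per affected outcome, against 37-41% with Holm and about 51% (5 of 32 affected) to 76% (24 of 32) with Benjamini-Hochberg.

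The absolute figures rest on f = 0.31 for every affected outcome, on an assumed number of affected outcomes, and on a between-groups test standing in for the planned growth model. Smaller secondary effects would lower all three columns. That Holm never rejects less than the fixed level depends on none of these assumptions.

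**What to change.** In Sample size and statistical analysis, list the outcomes that make up the 32 and say whether the two primaries are among them. Then name the error rate for the secondary family and match the procedure to it:

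- **If the false discovery rate is the aim:** replace the fixed 0.0015 by Benjamini-Hochberg at q = 0.05 and report adjusted p-values. State the price: the chance of at least one false positive rises to about 12-27% in the scenarios above, against about 1-4% with Bonferroni. Its guarantee also presumes independent or positively dependent tests.
- **If family-wise control is the aim:** use Holm at 0.05 and reword the purpose sentence. This gives up no error control and gains a little power.

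Fix the choice before unblinding, since choosing between procedures once results are known would undo the protection. The cost is a sentence or two of text and the list of outcomes, with no added patients or data.
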